### Data management

2.9.

A comprehensive data protection concept was developed in coordination with German pension insurance, which ensures data processing, the rights of the persons involved, as well as the technical and organizational measures for the secure and confidential collection, processing and storage of data. Researchers at the University of Lübeck only receive pseudonymized data from the insured persons and their children as part of the trend study. The generation of data within the process evaluation is anonymized. All questionnaire data is entered, checked and transferred to statistical software programs for further analysis. Data entry and data verification are performed by trained research assistants. Questionnaire data from the trend study is linked to administrative data from the insurance account using a pseudonym. Access to the data is limited to the authors and research assistants on the research team.

### Statistical methods

2.10.

Changes in the proportion of individuals with a migrant background in the samples will be analyzed using a Cochrane-Armitage test for trend (36). We will use unpaired t-tests for metric data, a Mann–Whitney U-test for ordinal data, and chi-square test for nominal data to describe differences between rehabilitants with and without migrant backgrounds in the samples. We will not perform interim analyses and did not specify a stopping rule. The results of statistical tests will be considered significant if the two-sided value of p of the test is less than 0.05. Process evaluation data is descriptively presented. A current version of Stata (StataCorp, College Station, Texas, USA) will be used to perform the analyses.

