### Medical rehabilitation for children and adolescents

1.3.

In general, children with chronic diseases in Germany are treated on an outpatient basis close to home by pediatricians or family doctors, in collaboration with other therapists (e.g., physiotherapists, child and adolescent psychotherapists). Outpatient treatment, however, may be not sufficient for some individuals. In these cases, the German social insurance system offers medical rehabilitation for children and adolescents (MRCA) (13). The legal basis for this is § 15a SGB VI. MRCA is intended to counteract the consequences of chronic illness, to enable schooling and vocational training without restrictions, and, in the long term, to prevent endangerment to, or the restriction of, gainful employment. In Germany, statutory health insurance and German Pension Insurance (GPI) are in principle equally responsible for medical rehabilitation. Despite this, the primary provider of MRCA services is the GPI. Every year, more than 32,000 requests for medical rehabilitation for children and adolescents are submitted to the German Pension Insurance. In Germany, medical rehabilitation for children and adolescents takes place almost exclusively in inpatient rehabilitation clinics. The most common reasons for using MRCA in 2018 were mental and behavioral disorders, followed by bronchial asthma, obesity and skin diseases such as neurodermatitis (14). Reliable data on the utilization of medical rehabilitation by children and adolescents with MB is not currently available, as the GPI administratively only records the nationality of rehabilitants. In terms of nationality, however, there is a clear underrepresentation of children and adolescents of non-German nationality (14). A recent study with adults shows that in addition to underutilization among persons without German nationality, underutilization by persons with a migration history can also be assumed (15). Possible reasons for this are utilization barriers such as insufficient language skills, a different understanding of illness, or insufficient knowledge of the German health care system (16).

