#### Trend study

2.5.1.

The primary outcome of the trend study on the utilization of rehabilitation is the proportion of children and adolescents with a migrant background among those undergoing rehabilitation who reside in Berlin or Hamburg. The migrant background is assessed in this study in accordance with the minimum indicator set for recording migration status (29).

We determine an individual as having a migrant background if they immigrated from another country and have at least one parent who was not born in Germany, or have two parents who immigrated and/or do not have German nationality.

This definition allows a differentiation between children with unilateral and bilateral migrant backgrounds (30). The information on the country of birth and nationality of the parents and the child required to map the migrant background is assessed through a questionnaire, and combined with data from the insured person’s account. The primary language, residence status, and duration of residence of the child and the child’s parents are also assessed.

In order to provide a description of the samples and to describe differences between children and adolescents with and without a migrant background in the samples, the health-related quality of life of the children and adolescents [KIDSCREEN-27 (31)], sociodemographic and socioeconomic information on the children and the parental home (32), perceived social support (33) and satisfaction with the rehabilitation service received will be collected through questionnaires as part of the trend study. The questionnaire data is supplemented by administrative data on medical rehabilitation (e.g., duration, and discharge diagnosis according to ICD-10) from parents’ insurance accounts. The data collected in the trend study is shown in Table 2.

**Table 2 tab2:** Data collected as part of the trend study.

Data	Source^2^	Sample 2020	Sample 2021	Sample 2022	Sample 2023
Migration history (34)		x	x	x	x
Nationality^1^	Questionnaire for parents/administrative data	x	x	x	x
Country of birth^1^	Questionnaire for parents	x	x	x	x
Primary language^1^	Questionnaire for parents	x	x	x	x
Duration of stay^1^	Questionnaire for parents	x	x	x	x
Residence status^1^	Questionnaire for parents	x	x	x	x
Socioeconomic status (31)	Questionnaire for parents	x	x	x	x
Social support (32)	Questionnaire for parents	x	x	x	x
Health-related quality of life (KIDSCREEN-27) (30)		x	x	x	x
Physical wellbeing	Questionnaire for parents/child	x	x	x	x

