#### Trend study

2.6.1.

A sample of 432 persons per year must be recruited in order to be able to demonstrate a change in the proportion of children and adolescents with a migrant background among the rehabilitants from 10 to 11%, 13, and 16% in the trend study [Cochran-Armitage test for trend (35)]. With a participation rate of 40% and 1,200 children and adolescents residing in Berlin or Hamburg receiving rehabilitation, power of 84% is needed to detect a significant trend. If the participation rate for persons without a migrant background is higher than for persons with a migrant background, the total sample size increases. Despite the observed reduced proportions of children and adolescents with a migrant background, the strength of the Cochran-Armitage test for trend is almost unchanged for the then-expected reduced trend.

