#### Trend study

2.7.1.

In the fourth quarter of 2020 to 2023, the German Pension Insurance identifies, based on administrative data, all insured persons residing in Berlin or Hamburg who have a child who received medical rehabilitation from the German Pension Insurance in the previous year (i.e., 2019, 2020, 2021, and 2022) and who was 17 years old or younger at the time of rehabilitation. These insured persons form the sample of the trend study.

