#### Trend study

2.8.1.

Trend study data will be generated through questionnaires and from administrative data from insured accounts. Insured persons identified by the German pension insurance will receive a cover letter, study information, a parent questionnaire, a child questionnaire (for the child who received medical rehabilitation), and a consent form for the use of administrative data at the beginning of the 4th quarter of 2020, 2021, 2022, and 2023. The questionnaires are pseudonymized. The questionnaires are returned to the University of Lübeck by the insured persons and electronically recorded there. The declaration of consent is sent by the insured persons to the German Pension Insurance, who send one reminder after four weeks. If consent is given, German pension insurance sends a pseudonymized data set with data from the insured persons’ accounts to the University of Lübeck, where this administrative data is linked to the questionnaire data using the pseudonym.

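### The only effectiveness test is run on survey responders, so a migrant response rate that shifts between waves could create or hide a trend; full-frame nationality counts would be a cheap check

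*Protocol article*

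**What the plan says.** Section 2.5.1 (Outcomes, Trend study) defines the primary outcome as "the proportion of children and adolescents with a migrant background among those undergoing rehabilitation who reside in Berlin or Hamburg". Migrant background is established by questionnaire, combined with account data, so it is known only for families who answer.

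Section 2.10 (Statistical methods) fixes the test: "Changes in the proportion of individuals with a migrant background in the samples will be analyzed using a Cochrane-Armitage test for trend". Results are "considered significant if the two-sided value of p of the test is less than 0.05". No adjustment for non-response is attached to the test.

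Section 2.6.1 (Sample size) plans for a change "among the rehabilitants from 10 to 11%, 13, and 16% in the trend study" and gives its power under the condition "With a participation rate of 40"% of 1,200 rehabilitants. It raises lower participation by migrant families, but only for its effect on sample size and power, and as a fixed gap.

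On the administrative side, section 1.3 says "the GPI administratively only records the nationality of rehabilitants". Section 2.7.1 says the insurer "identifies, based on administrative data, all insured persons residing in Berlin or Hamburg" who qualify, each year. Section 2.8.1 limits the release of individual account data: "If consent is given, German pension insurance sends a pseudonymized data set".

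The Conclusion expects the trend study to show whether utilization rose, and expects changes to be related to how the modules were implemented.

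**The concern.** The outcome concerns all rehabilitants of a year; the test concerns those who return a questionnaire. The two agree over time only if migrant response relative to non-migrant response stays the same across the four waves. If that ratio moves, the share among responders moves even when use of rehabilitation does not.

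There is a conceivable route for this. The first survey describes 2019, before the campaign. Later surveys go out during or after a campaign that explains rehabilitation in families' own languages and helps with application forms, and the survey itself arrives by mail through the pension insurance. Some families might become readier to answer without any change in use.

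This is the only effectiveness test in the plan, and the test as stated cannot separate response drift from a change in use. Drift upwards would be read as success; drift downwards could conceal a real effect.

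**Working it through.** **Inputs from the article.** Four waves; 1,200 rehabilitants per year; 40% participation, so 480 responders per wave; 432 stated as required; planned shares 10, 11, 13 and 16%; two-sided 5% level.

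**Formulas.** Scores x = 0, 1, 2, 3; n_t responders and p_t observed share in wave t; x̄ and p̄ are the n-weighted means.
- T = Σ n_t p_t (x_t − x̄)
- V0 = p̄(1 − p̄) Σ n_t (x_t − x̄)²
- V1 = Σ n_t p_t (1 − p_t)(x_t − x̄)²
- P(significant rise) = Φ[(T − 1.96√V0)/√V1]

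**The plan's own figure.** With n = 480, T = 480 × 0.10 = 48, V0 = 0.125 × 0.875 × 480 × 5 = 262.5 and V1 = 267.7. Then (48 − 1.96 × 16.20)/16.36 = 0.99, giving 84.0%. With n = 432 the result is 80.0%. Both planning figures reproduce: 432 is the size for 80% power, and 84% is the power at 480.

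**No true change, drifting response.** Assumptions: true share 10% in every year (120 migrant and 1,080 non-migrant rehabilitants), non-migrant response fixed at 40% (432 responders), migrant response r_t changing linearly. The observed share is p_t = 120 r_t / (120 r_t + 432).

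Worked case, 28 to 40%: migrant responders 33.6, 38.4, 43.2, 48.0; observed shares 7.22, 8.16, 9.09, 10.00%. T = 21.93, V0 = 186.4, V1 = 185.5; (21.93 − 1.96 × 13.65)/13.62 = −0.35, giving 36%.

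| Migrant response, first to last wave | P(significant rise), nominal 2.5% |
|---|---|
| constant 28% | 2.5% |
| 28 to 30% | 4.8% |
| 28 to 32% | 8.3% |
| 28 to 34% | 13% |
| 28 to 40% | 36% |
| 24 to 36% | 40% |

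**A true rise, opposite drift.** True shares 10, 11, 13, 16%; migrant to non-migrant response ratio 0.80, 0.75, 0.70, 0.65. Observed shares become 8.16, 8.48, 9.47, 11.02% and power is about 35%. A constant ratio of 0.80 would already lower power from 84% to about 76%, so the drift accounts for the fall from there.

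**What nationality data could do.** Assume a fraction f of migrant families is non-German, all of them counting as migrant, with the same drift in German and non-German migrant families. The calibrated share is s + (1 − s)q_t, where s = 0.10f comes from the frame and q_t is the migrant share among German responders. For 24 to 36% and f = 0.5, q runs from 14.4/446.4 = 3.23% to 21.6/453.6 = 4.76%. The calibrated share then runs from 8.06 to 9.52%, against 6.25 to 9.09% uncalibrated. By simulation, with the post-stratified variance, false rises fall from about 40% to about 17%. They fall to 26% if f = 0.3 and to just under 10% if f = 0.7. They return to nominal if drift is confined to non-German families.

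A nationality trend test on the whole frame (1,200 per year) rejects in 5% of trials, two-sided, when nothing changes, whatever the response drift. For a proportional rise from 10 to 16%, with f stable at 0.3, 0.5 or 0.7, its power is 68, 89 or 97%.

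**The case against.** The strongest reply is that bias needs a changing gap, not a low response rate, and that nothing in the article shows one. The mailing, the single reminder and the survey quarter are the same every year, which favours comparable waves. The drift sizes are chosen, and 24 to 36% is a relative rise of one half. Campaign reach is limited: 48 individual consultations in total, and events for about 2,400 people in two cities who need not be rehabilitants' families. Even if exposure doubled a family's response from 28 to 56%, a move to 40% would need (40 − 28)/(56 − 28) = 43% of migrant rehabilitant families to be exposed. All of this stands, and it is why the smaller drifts belong in the table.

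A reader might infer that the campaign will inflate response and that the primary test is therefore invalid. The article supports only that this could happen. A reader might also infer that a nationality-weighted test should become primary. It should not: about 17% false rises remain in the case above, section 1.3 itself treats nationality as an insufficient record of migrant background, and the footnote to Table 2 says administrative data come from the applying parent's account, whereas the outcome uses the child and both parents.

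Finally, non-response weighting and participation tables are often left to a fuller plan, so their absence alone is no fault. What remains is that the article itself fixes an unadjusted test on responders, takes up differential participation only as a fixed gap affecting size and power, and reads the result as utilization.

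**Conclusion.** The point holds as a conditional weakness. The type I error for a change among all rehabilitants is nominal if relative response is stable. It is modestly inflated by small drifts (about 5 to 8% upward, against 2.5%, for rises of two to four percentage points) and seriously inflated by larger ones (13% for six points, 36% for twelve from 28%). Drift in the other direction can reduce power to about 35%. These sizes rest on an assumed constant true share of 10% (or the planned rise, for the power figure), non-migrant response of 40% and linear drift. The article gives no response rates by migrant background, and 40% is a planning value. The planning figures of 432 and 84% are arithmetically sound. The case is for an inexpensive safeguard around the primary test, not for replacing it.

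**What to change.** Keep the Cochran-Armitage test on responders as primary. In addition:

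1. Ask the three pension insurance providers for anonymous aggregate counts, per rehabilitation year, of all rehabilitants in the frame by recorded nationality, and by city and age band if available. State whose nationality the record holds (child or applying parent).
2. Report participation by nationality and year.
3. Pre-specify two sensitivity analyses: a trend test on nationality in the full frame (about 1,200 per year, free of survey non-response), and a trend test on responders calibrated to each year's frame nationality totals.
4. State that a trend will be attributed to utilization only if these analyses agree with the primary test in direction.

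The cost is one aggregate request per year and a short additional analysis. The article neither plans nor excludes such counts, so their availability has to be confirmed; because they are aggregates, they would not need the individual data that section 2.8.1 releases only with consent. The limitation to declare is that nationality covers only part of migrant background, so agreement strengthens the reading of a trend but does not prove it.

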## Discussion

3.

The aim of our evaluation is to describe the implementation of a complex multimodal information campaign to improve the utilization of medical rehabilitation by children and adolescents with a migrant background, and to test the effectiveness of this intervention. The intervention aims to improve health-related support and information provision for a particularly vulnerable population group, and thus to make a lasting contribution to reducing social inequality in health care in Germany. The intervention presented here is a participatory measure that actively involves migrants in the process of providing information, in line with recent WHO recommendations (17), and aims to sustainably anchor the knowledge and skills imparted in migrant communities. The process evaluation and trend study will generate data that will allow a detailed assessment of the implementation and success of the described information campaign. In this way, the project will enable the intervention to be adapted and further developed for similar objectives, for example with regard to other healthcare services or other regions. Up-to-date information on the information campaign and the study can be found on the website www.mimi-reha-kids.de. The results of our study will all be published as articles in peer-reviewed journals and at conferences. The authors of this protocol will write the final study publications. The use of professional authors is not anticipated.

## Conclusion

4.

The study described in this protocol will provide comprehensive data on which persons can be reached within the different modules of the multimodal information campaign and how the information campaign and its different modules are perceived by the participants. The results of the trend study will also provide information on whether the utilization of medical rehabilitation by children and adolescents with a migrant background could be increased over the intervention period at the intervention sites. Thus, possible changes in utilization can be related to the specific implementation of the modules of the information campaign. These data can help organizations and institutions to adapt or further develop the multimodal information campaign or specific modules for other regions in Germany or other countries.

## Trial status

Process evaluation and cross-sectional surveys of the trend study have begun and will continue.

## Ethics statement

The studies involving human participants were reviewed and approved by Ethics Committee of the University of Lübeck. Written informed consent to participate in this study was provided by the participants’ legal guardian/next of kin.

## Abbreviations

EU: European Union
EMC: Ethno-medical Center
GPI: German Pension Insurance
ICD: International Classification of Diseases
IOM: International Organization for Migration
MB: Migrant background
MRCA: Medical Rehabilitation for Children and Adolescents
OECD: Organization for Economic Co-operation and Development
WHO: World Health Organization
SGB: Sozialgesetzbuch (Social Security Code)
TIDieR: Template for Intervention Description and Replication
